## Abstract

**Background:**

Diabetic nephropathy (DN) is the major complication of diabetes; proteinuria is the hall mark of DN. Currently, the treatment for proteinuria is mainly limited to angiotensin converting enzyme (ACE) inhibitors or angiotensin II receptor blockers (ARBs). According to Traditional Chinese Medicine (TCM) theory, Chinese medicinals ‘securing essence and tonifying the kidney’ may be appropriate for proteinuria. The most promising Chinese medicinals and formulae are introduced in the present study to form a potent formula for DN proteinuria. To make oral administration convenient, the formula will be processed in the form of granules.

**Methods/design:**

A randomized, multi-center pilot trial will be conducted. Forty eight participants with DN will be randomly assigned to one of four treatment groups:

1. A granule group, at 10 grams, three times daily (G10 group, n = 12);

2. A granule group, at 20 grams, three times daily (G20 group, n = 12);

3. A decoction group (D group, n = 12); and

4. An irbesartan group (Aprovel group, n = 12).

The following outcome measures will be used: the percentage change of the albumin-to-creatinine ratio; and the changes in serum creatinine, glomerular filtration rate, fasting plasma glucose and hemoglobulin from baseline to the end of the trial.

**Discussion:**

It is notable that most published clinical trials which assessed the efficacy of TCM on DN were of poor methodology and, therefore, their results have been invalidated. It is necessary to carry out well-designed clinical trials to provide sound evidence. The present trial is a study with potentially great value, for it will provide the parameters for future randomized, placebo-controlled, clinical trials with large sample sizes.

**Trial registration:**

The trial is registered on the Chinese Clinical Trial Registry: ChiCTR-TRC-12002718 (http://www.chictr.org/cn/proj/show.aspx?proj=3820).

## Background

The prevalence of diabetic nephropathy (DN) in China is not very clear; however, in Beijing, the city which has the best medical service in China, the incidence of DN in patients with type 2 diabetes is 35.7% and that of microalbuminuria is 13.6% [1].

In Traditional Chinese Medicine (TCM) theory, the kidney is a paramount organ. It stores essence and the essence transforms *Qi* and produces blood. In addition, the kidney is the source of genuine *Yin* and genuine *Yang*. It is called ‘the prenatal base of life’ in TCM textbooks [2]. In the TCM system, there are many Chinese medicinals classified as tonifying and replenishing medicinals. Many of them have the effects of replenishing *Qi* of the kidney or tonifying kidney *Yang*.

We have known that DN is the major complication of diabetes and proteinuria is the hallmark of DN. DN is also defined by increased urinary albumin excretion (UAE) in the absence of other renal diseases, which is categorized into stages according to the level of UAE, that is, microalbuminuria (30 to 299 mg/24 hours) and macroalbuminuria (300 mg/24 hours or greater) [3]. Currently, the treatment for proteinuria is largely limited to angiotensin converting enzyme (ACE) inhibitors or angiotensin II receptor blockers (ARBs) [4]. Although the clinical beneficial effects of many ACE inhibitors or ARBs have been established [5], the efforts of looking for new drugs for DN that involve reducing proteinuria never stop. For example, many researchers investigated astragalus for the treatment of DN and the results seemed intriguing. Zhang et al. [6] systematically reviewed published animal experiments that had assessed the renal protective effects of astragalus in diabetic rat models. Their results showed significant beneficial effects of astragalus involving improved fasting blood glucose levels, glomerular filtration rate (GFR), urinary albumin excretion rate, and thickness of the glomerular basement membrane. Hong and co-workers [7] reported that astragalus might ‘play protective roles in diabetic nephropathy through multiple pathways at the gene level’.

Is TCM really able to lower proteinuria in patients with DN? Current evidence has tried to address this issue, but the picture remains unclear [8]. The present research looks at the DN-lowering proteinuria effect of TCM to answer this question. To evaluate the effects of TCM accurately, the most promising Chinese medicinals and formulae are used in the present study to form a potent formula for the treatment of proteinuria of DN.

Because proteinuria, in TCM theory, results from the leakage of the essence of the human body due to an insufficiency of the kidney, it is promising to look for Chinese medicinals that secure the essence and tonify the kidney for the treatment of proteinuria. A typical herb that secures essence and tonifies the kidney is used in the present study, Flastem Milkvetch Seed. A famous classical formula securing the essence and tonifying the kidney is also introduced in the present study for the treatment of proteinuria (Water-land Two Elixirs). It consists of two Chinese medicinals, Gordon Euryale Seed and Cherokee Rose Fruit. The first ingredient is grown in water and the second one is grown on land, which is the reason why it is named ‘Water-land.’ This formula is very effective for treating conditions such as spermatorrhea and enuresis [9]. However, only securing essence is not enough; because *Yin/Yang* has been damaged, it is essential to repair the balance between them.

There is a therapeutic strategy in TCM theory, namely, using ‘cool’ and ‘warm’ herbs together to balance *Yin/Yang*; this strategy is introduced in the present study. As the most conspicuous topic in the area of TCM treatment for DN, astragalus may be a very potent Chinese medicinal for proteinuria; therefore, it is also used in the present study. Both basic and clinical studies have demonstrated that astragalus could exert beneficial effects on DN [10-12]. An *in vitro* study investigated the effect of calycosin and calycosin-7-O-β-D-glucoside. These two major isoflavonoids in astragalus were tested with high glucose-induced rat mesangial cell proliferation and advanced glycation end product (AGE)-induced human glomerular endothelial cell apoptosis. The results suggested that both isoflavonoids had a significant therapeutic potential to modulate the development and/or progression of DN [10]. Zhang and his co-workers studied the effects of astragalus polysaccharide (APS), an aqueous extract from the astragalus membranaceus roots, on gene expressions of nuclear factor-kappaB (NF-kappaB) and an inhibitory protein of NF-kappaB (IkappaB) in experimental DN rats induced by streptozotocin. The results showed that APS improved proteinuria and renal function and that the mRNA level of NF-kappaB in renal cortex was decreased and IkappaB mRNA expression was raised by APS [11]. A randomized controlled trial showed that astragalus, in combination with captopril, could significantly reduce UAE [12]. However, astragalus is an herb of warm properties and has the capacity to upset the balance of *Yin/Yang*. Coptidis, is an herb of cool properties and is used to counteract the potential harm caused by astragalus. Coptidis is used for proteinuria because not only does it have centuries of practice-based recognition as a reliable TCM remedy for diabetes mellitus but its potential as a treatment for DN has been established in recent evidence-based supportive research. Liu et al. [13] evaluated the effects of compound Rhizoma Coptidis capsule (CRCC) on early DN in rats induced by streptozotocin. Their results showed that CRCC could reduce the levels of fasting plasma glucose (FPG), blood urea nitrogen (BUN), serum creatinine (Scr), proteinuria, the expression of transforming growth factor-beta1 and IV-C proteins, and alleviate pathological lesions in renal tissue of diabetic rats with nephropathy.

As a result, five Chinese medicinals are used in the present study for the treatment of proteinuria: astragalus, coptidis, Flastem Milkvetch Seed, Gordon Euryale Seed and Cherokee Rose Fruit (the Latin name and English name of the Chinese herbs mentioned in the article are shown in Table 1).

**Table 1 T1:** **Traditional Chinese Medicinal Herbs used in *****Huang Qi Elixir *****formula/granule**

**PinYin name**	**Latin name**	**English name**	**Daily decoction dose**	**Dose per 1,000 g granule**
Huangqi	*Radix Astragali*	Astragalus/Astragalus membranaceus	30 g	500g
Shayuanzi	*Semen Astragali Complanati*	Flastem Milkvetch Seed	30 g	500g
Huanglian	*Rhizoma Coptidis*	Golden Thread	10 g	167g
Jinyingzi	*Fructus Rosae Laevigatae*	Cherokee Rose Fruit	15 g	250g
Qianshi	*Semen Euryales*	Gordon Euryale Seed	15 g	250g

One of the most obvious inconveniences of TCM is the preparation. It is very difficult to ask patients to decoct TCM several times daily for a long time and, therefore, this research group decided to make the formula in the form of granules (the ingredients are shown in Table 1). The granules are processed using the following methods: first, *coptidis* is ethanol extracted; second, the other five herbs are decocted together and then aqueous extracted; third, the concentrate from the previous two steps is mixed and then spray-dried. The granule is a 10 g/package.

### Objective

The aim of this clinical study is: (1) to evaluate if the efficacy of *Huang Qi* Elixir for proteinuria in patients with microalbuminuria is equivalent to that of the decoction; (2) to establish the working dose of the TCM granule; and (3) to evaluate the difference in efficacy between the TCM granule and the ARB (that is, irbesartan).

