### Randomization and intervention

The study has four arms. After enrollment, 48 participants who meet the inclusion criteria will be randomly assigned to either: 1) granule group, 10 grams three times daily (G10 group, n = 12); 2) granule group, 20 grams three times daily (G20 group, n = 12); 3) the decoction group (D group, n = 12); or 4) the irbesartan group (Aprovel group, n = 12). The treatment course is 12 weeks. The randomization sequence will be generated with an SAS software package by the Good Clinical Practice (GCP) Center of the Teaching Hospital of Chengdu University of TCM and will be concealed and disseminated using opaque envelopes.

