### Outcome measures

#### Primary outcome

The primary outcome, percentage change in ACR from baseline, will be measured at week 12. ACR will be measured with a spot urine test, every four weeks; 15 to 20 ml spot urine samples will be collected at each visit to assess albuminuria.

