### Statistical methods

Statistical analyses will be conducted based on an intention-to-treat population. Participants who take at least one dose of drug and have one value on treatment comprise the full-analysis set (FAS) and those who complete a 12-week treatment comprise the per-protocol set (PPS). Missing data will be imputed with the use of the last-observation-carried-forward method, whereby missing values will be replaced by the last non-missing value. Repeated measures and multivariate analysis of variance of the general linear model will be applied to determine the changes in GFR, Scr and FPG at each visit. Percentage reduction from baseline in ACR and changes from baseline in HbA1c will be summarized and comparisons will be made by using a one-way analysis of variance.

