### Sample size

Each arm will only include 12 subjects, for this is just a pilot trial aimed at exploring some parameters for a future clinical trial with a large sample size.

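### Objective 1 asks whether the granule is equivalent to the decoction, but the only test named for ACR is a test of difference, which cannot answer that

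*Protocol article*

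**What the plan says.** The Objective section of the protocol article lists three aims. The first opens with "to evaluate if the efficacy of" the granule and asks whether the "Elixir for proteinuria in patients with microalbuminuria is equivalent to that of the decoction". The third, on irbesartan, is worded differently: "to evaluate the difference in efficacy between the TCM granule and the ARB". So the article itself uses one term for the decoction comparison and another for the irbesartan comparison.

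Under Primary outcome: "The primary outcome, percentage change in ACR from baseline, will be measured at week 12". Under Statistical methods, for percentage reduction in ACR and change in HbA1c, "comparisons will be made by using a one-way analysis of variance". The repeated-measures and multivariate models in the same section "will be applied to determine the changes in GFR, Scr and FPG at each visit"; they are not assigned to ACR.

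Under Randomization and intervention, "48 participants who meet the inclusion criteria will be randomly assigned to either" one of four arms of 12: granule 10 g, granule 20 g, decoction, irbesartan. Under Sample size: "Each arm will only include 12 subjects, for this is just a pilot trial aimed at exploring some parameters". No power is claimed.

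**The concern.** An equivalence question and a difference test have opposite null hypotheses. Analysis of variance starts from equal means and looks for evidence against that. Equivalence starts from the means being at least some margin apart and looks for evidence that they are closer. Failing to reject in the first setting proves nothing in the second, because failure can come from small numbers as easily as from similar effects. A significant four-arm F test would not settle the matter either, since it does not say which arms differ.

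The first-listed aim therefore has no stated analysis that could answer it. Nor does the aim say which of the two granule arms is to be compared with the decoction. At stake is how the granule-decoction result is reported: with 12 per arm, no significant difference is a likely finding even when the true difference is material.

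**Working it through.** **The plan's own figure.** The article gives no power, SD, effect size, significance level or margin, so there is no sample size calculation to reproduce. The one check available agrees: 4 × 12 = 48.

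**Inputs.** From the article: 12 per arm, four arms, hence 48 − 4 = 44 residual degrees of freedom in the analysis of variance, or 22 if only two arms are used. Assumed, because the article gives none: two-sided 5% level, no dropout, SD of the log-ACR change of 0.4, 0.6 or 0.8, and a true granule/decoction ratio of 1.35 as an example of a material difference.

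**Step 1: precision in SD units.** Standard error of a difference between two arms = SD × √(2/12) = 0.408 SD.
- 24 patients, 22 df: 95% half-width = 2.074 × 0.408 = 0.85 SD; 90% half-width = 1.717 × 0.408 = 0.70 SD.
- Variance pooled over four arms, 44 df: 95% half-width = 2.015 × 0.408 = 0.82 SD.

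**Step 2: precision as a ratio.** 95% CI factor = exp(2.015 × 0.408 × SD), with 44 df.
- SD 0.4: exp(0.329) = 1.39
- SD 0.6: exp(0.494) = 1.64
- SD 0.8: exp(0.658) = 1.93

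**Step 3: how often a material difference is non-significant.** The true log ratio is ln 1.35 = 0.300. The noncentrality of the pairwise t test is 0.300 / (0.408 × SD). For the four-arm F test, one arm is taken to differ by this amount from three equal arms, with noncentrality 12 × 0.75 × (0.300/SD)² on 3 and 44 df.

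| SD of log change | t noncentrality | Pairwise test non-significant | Four-arm F test non-significant |
|---|---|---|---|
| 0.4 | 1.84 | 56% | 59% |
| 0.6 | 1.23 | 78% | 80% |
| 0.8 | 0.92 | 85% | 87% |

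**Step 4: what an equivalence test could do at this size.** Two one-sided tests at 5% each (the same as requiring the 90% CI to lie inside the margin), true ratio 1, 44 df, by simulation:

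| Margin for the ratio | SD 0.4 | SD 0.6 | SD 0.8 |
|---|---|---|---|
| 0.80 to 1.25 | 0.2% | 0% | 0% |
| 0.70 to 1.43 | 39% | 1% | 0% |
| 0.50 to 2.00 | 99% | 75% | 34% |

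In SD units with 22 df, 12 per arm reaches 80% power only at a margin near 1.23 SD. The chance of success runs from nil to near certainty, depending on a margin and an SD that the article does not give.

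Steps 2 to 4 work on the log scale; the stated outcome is percentage change. They show how imprecise the comparison is, not the exact operating characteristics of the planned analysis.

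**The case against.** The article is a condensed account, and a margin, a CI rule or planned contrasts may sit in a full protocol or analysis plan that is not shown. That stands as far as it goes: the absence of a margin here is not a fault in itself. It does not remove the mismatch, because the article does name the method for the primary outcome, and that method cannot answer its first aim.

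The pilot status is declared openly, and Sample size claims no power. That also stands. Twelve per arm is not wrong, and it does not strictly contradict the aim: asking to evaluate whether something is so is loose wording that can coexist with an exploratory purpose. It is a tension, eased by rewording.

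A reader might infer that a non-significant result will be reported as equivalence, or that the later large trial will rest on such a reading. The article says neither. It gives convenience as the reason for making granules and describes the successor as placebo-controlled, without making it depend on an equivalence result.

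A reader might also infer that 12 per arm could never show equivalence. That depends on the margin: within 0.50 to 2.00 it often could under the smaller assumed SDs, within 0.80 to 1.25 hardly ever.

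**Conclusion.** The point holds as a mismatch between a stated objective and a stated method. Objective 1 concerns equivalence; the only test named for ACR is a test of difference, and no other criterion is given. This follows from the text and needs no assumption.

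Its practical size does need assumptions. The half-width of about 0.85 SD rests only on 12 per arm, a 95% level and no dropout. The factors of 1.39 to 1.93 and the 56% to 85% rest on the assumed SDs and, for the latter, on a 35% true difference. Within that range, non-significance is more likely than not even when the granule is materially worse, so it would carry little information about equivalence.

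**What to change.** - **Objective 1:** reword it as estimating the granule-decoction difference (or ratio) in week-12 ACR change, separately for each granule arm, with its 95% CI, to inform the later trial.
- **Statistical methods:** report that CI as the result for objective 1, and add one sentence that a non-significant analysis of variance or contrast will not be taken as equivalence.
- **If the word equivalent is kept:** allow it only when the 90% CI lies inside a justified margin fixed before database lock, and report that the chance of success with 12 per arm depends on that margin and on the SD.

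The cost is the wording of one objective and a sentence or two in Statistical methods. No patients, visits or measurements are added. The downside is a more modest stated claim.

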## Discussion

Many clinical trials have been carried out to evaluate the efficacy of TCM for DN [14,15]. Liu et al. [16] systematically reviewed randomized controlled trials evaluating the efficacy and safety of astragalus in the treatment of DN. Their results included 33 RCTs and one quasi-RCT involving 2,356 patients and showed that it ‘had some effects on the decrease of the 24-hour urinary albumin excretion rate (UAER), 24-hour urinary protein, Scr, and BUN, and also on the improvement of Ccr’ (p. 727). They concluded that it ‘has some effect and is relatively safe in treating patients with DN’. Another study [17] evaluated the efficacy and safety of a TCM capsule, *Xuezhikang,* in the treatment of DN. The results of meta-analyses showed that it ‘was superior to routine treatment in decreasing 24-h urinary protein, microalbuminuria and UAER’. However, ‘due to a high risk of selection bias and detection bias in the included studies, the evidence is insufficient to determine the effect of *Xuezhikang*’.

Obviously, it is notable that most published clinical trials which assessed the efficacy of TCM on DN were of poor methodology, and, therefore, their results have been invalidated. It is necessary to carry out well-designed clinical trials to provide sound evidence. The present clinical study introduces those promising and classical herbs and formulae into the treatment of microalbuminuria. To make administration convenient, a TCM decoction will be processed in the form of granules. The present trial is a study of great value for it will provide important parameters for a future randomized, placebo-controlled, clinical trial with a large sample size.

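### Objective 1 asks whether granule and decoction are equivalent, but ACR is compared only by a one-way ANOVA, which tests for a difference, and the objective does not say which granule arm it concerns

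*Protocol article*

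**What the plan says.** - **Aim.** Objective 1 (Objective section) asks whether the efficacy of *Huang Qi* "Elixir for proteinuria in patients with microalbuminuria is equivalent to that of the decoction". Objective 2 is to find the working dose of the granule. Objective 3 concerns a difference between granule and irbesartan. The protocol therefore uses equivalence wording for one comparison and difference wording for another.
- **Analysis.** Under Statistical methods, percentage reduction in ACR is to be summarised and "comparisons will be made by using a one-way analysis of variance". The repeated-measures and multivariate model is assigned to GFR, serum creatinine and fasting glucose, not to ACR.
- **Arms.** There are two granule arms: 10 g three times daily, and "granule group, 20 grams three times daily (G20 group, n = 12"). The comparator is given only as "the decoction group (D group, n = 12"), with no dose at that point.
- **Formulation.** The Discussion presents the granule as a more convenient form of the decoction: "To make administration convenient, a TCM decoction will be processed in the form of granules". Table 1 lists each herb under "Daily decoction dose" and "Dose per 1,000 g granule". The text below it says that coptidis "is ethanol extracted; second", the remaining herbs are decocted and aqueous-extracted.
- **Size.** The Sample size section fixes 12 per arm because the trial is a pilot meant to supply parameters for a larger one. It gives no power, SD or margin.

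**The concern.** An equivalence question is answered by showing that the difference lies within limits that matter. A one-way ANOVA asks whether the arm means differ at all. With 12 per arm, failing to find a difference is the likely result even when a material one exists, so a non-significant result could be read as showing that the granule matches the decoction when a large difference is still possible. In the other direction, a significant four-arm F may come entirely from irbesartan, which has no part in objective 1.

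The objective also leaves the granule arm open. If the arms carry different amounts of herb, the two possible comparisons answer different questions, and the choice between them could be made after the results are seen. The later trial needs the granule-versus-decoction difference and its precision, and the plan as stated does not commit to reporting either.

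**Working it through.** There is no power calculation to reproduce: the only stated figure is 4 × 12 = 48. The protocol gives neither an SD nor a margin, so all differences below are in SD units of percentage change in ACR.

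**1. Which granule arm matches the decoction (Table 1)**

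Crude herb per day = granule g/day × (g herb per 1,000 g granule) ÷ 1,000. G10 is 3 × 10 = 30 g/day of granule and G20 is 3 × 20 = 60 g/day.

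| Herb | Decoction, g/day | Per 1,000 g granule | G10, g/day | G20, g/day |
|---|---|---|---|---|
| Huangqi | 30 | 500 | 15 | 30 |
| Shayuanzi | 30 | 500 | 15 | 30 |
| Huanglian | 10 | 167 | 5.01 | 10.02 |
| Jinyingzi | 15 | 250 | 7.5 | 15 |
| Qianshi | 15 | 250 | 7.5 | 15 |
| Total | 100 | 1,667 | 50 | 100 |

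If arm D receives the Table 1 daily dose, G20 matches it herb by herb and G10 gives half. The match is in crude herb only, because coptidis is extracted with ethanol for the granule.

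**2. Precision of G20 minus decoction**

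- 12 per arm, pooled error on 4 × 11 = 44 df: SE = √(2/12) = 0.408 SD.
- 95% half-width: 2.015 × 0.408 = 0.82 SD.
- 90% half-width, which corresponds to two one-sided 5% tests: 1.680 × 0.408 = 0.69 SD. If the observed difference were exactly zero, and the SD as assumed, true differences up to 0.69 SD would still not be excluded.
- 10 per arm analysed, 36 df: 2.028 × √(2/10) = 2.028 × 0.447 = 0.91 SD.

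**3. How often a real difference is missed (two-sided 5%)**

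Let the decoction arm differ by *d* SD from three otherwise equal arms.

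- Pairwise contrast: noncentral *t* on 44 df, noncentrality *d*/0.408.
- Four-arm F: noncentral F(3, 44), with λ = 12 × [(3*d*/4)² + 3(*d*/4)²] = 9*d*².

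| True difference *d* | Missed by contrast | Missed by F |
|---|---|---|
| 0.5 SD (λ = 2.25) | 77.6% | 80.3% |
| 0.82 SD (λ = 6.05) | 49.8% | 51.7% |
| 1.0 SD (λ = 9) | 33.1% | 33.2% |

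**4. A significant F with no granule–decoction difference**

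Let G10, G20 and decoction be identical and irbesartan differ by 1 SD. Then λ = 9 and P(F significant) = 1 − 0.332 = 67%. A simulation of 100,000 trials gave 66.7%.

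**5. Could an equivalence test be kept at this size?**

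Power of two one-sided 5% tests at 12 per arm, true difference zero, 44 df: about 0% for a margin of 0.5 SD, 14% for 0.75 SD, 56% for 1.0 SD and 95% for 1.5 SD. Only a very wide margin would be workable.

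**The case against.** The strongest reply is that the article does not restrict ACR to an omnibus F. It speaks of comparisons in the plural, and pairwise contrasts with intervals are details that an article commonly leaves to the full protocol or analysis plan. That has force against step 4: the 67% matters only if the F-test alone is used. It does not rescue objective 1, because a pairwise difference test from the same ANOVA cannot show equivalence either (step 3, contrast column).

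Second, the trial is a declared pilot and nowhere says that a non-significant result will be taken as equivalence. That is true, and 12 per arm is not the complaint. But equivalence is a stated aim, and pilot status makes such a conclusion harder to support.

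Third, with dose-finding as objective 2, both granule arms may be relevant to objective 1, and Table 1 lets a reader work out that G20 is the matched arm. Both points are fair: G10 against decoction is worth reporting, provided that it is labelled as a half-dose comparison. The objective should still say which comparison it concerns.

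Fourth, Table 1 very probably does give arm D's dose, so stating it in the arm description is a small clarification. The processing text also refers to five other herbs after coptidis, whereas Table 1 leaves four. If that is more than a slip, the crude-herb match would need rechecking.

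Finally, the F-test miss rates assume that decoction differs from three equal arms. Other patterns would give other F-test figures, but the confidence-interval widths do not depend on the pattern.

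**Conclusion.** The concern holds. The protocol states an equivalence aim and fixes a difference test for the outcome that aim concerns. Neither the F-test nor a pairwise test from it can support equivalence at 12 per arm. The 95% interval for G20 minus decoction is ±0.82 SD with full data and ±0.91 SD with 10 per arm, and a true 0.5 SD difference goes undetected in roughly four trials out of five. Objective 1 also leaves open two comparisons that differ twofold in crude herb.

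The figures assume a common SD, normal errors, pooled error from four arms and, except where 10 per arm is stated, no dropout. The dose match assumes that arm D receives the Table 1 daily dose. The mismatch between aim and test needs none of these assumptions. The point should be corrected; it does not call the trial's conduct into question.

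**What to change.** - Reword objective 1: to estimate the difference in percentage change in ACR at week 12 between G20 and the decoction, matched for crude herb content.
- Add to Statistical methods: the G20 minus decoction contrast will be reported from the one-way ANOVA with its 95% confidence interval, and no conclusion of equivalence will be drawn from this pilot.
- Report G10 minus decoction, if wanted, as a secondary estimate with its confidence interval, labelled as a comparison at half the crude-herb dose.
- State the daily dose in the description of arm D.
- Leave objectives 2 and 3 unchanged.

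The alternative is to keep the equivalence aim, name the arm and set a margin in advance. At 12 per arm that would work only with a margin well above 1 SD, so estimation is the better choice here.

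The cost is a reworded objective, one sentence of method and one dose. Arms, visits, outcome scale and sample size do not change. The price is that the pilot can make no equivalence claim, which its size could not have supported in any case.
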